# **Introduction**

Age-related and disease-related loss of muscle mass and strength induces important negative pathophysiological changes in the elderly, such as reduction in the ability to maintain balance, changes in glucose homeostasis, thermoregulation and bone nutrition, and reduced basal metabolic rate/energy production. These consequences contribute considerably to the progression of loss of self-sufficiency on account of the reduction in both dynamic and static muscle strength, increase in morbidity, and susceptibility to multiple disorders; overall, they contribute to a general condition called sarcopenia. A number of factors may contribute to its onset. Sudden and important muscle mass loss is a common occurrence following a period of immobility or reduction in mobility, such as admission to hospital, and only three days of bed rest can result in the loss of >1 kg of muscle mass in elderly patients. Nonetheless, sarcopenia is a disease that frequently occurs in the community where a sedentary lifestyle and inadequate dietary intake of proteins and specific micronutrients (e.g. vitamin D) can trigger and accelerate its progression.

Taking into account the time trends in life expectancy, the treatment of this disease is a key issue with important pharmaco-economic implications. Interventions should modulate anabolic and catabolic pathways within the muscle but, despite a substantial increase in the understanding of the molecular basis, approved agents are limited and not free of side effects. At present, the basic treatment of sarcopenia consists in targeting muscle mass and function through physical exercise (resistance training), optimization of protein intake and vitamin D supplementation.

In respect to nutritional intervention, particularly to optimize protein intake in advanced age, attention should be paid not only to the amount of proteins provided but also to their quality. Whey proteins have proved to enable a greater anabolic stimulation due to their faster digestion – resulting in a more rapid increase in plasma amino acid levels – and high content in essential amino acid. Among essential amino acids, leucine has been found to stimulate anabolism independently. It has been recommended that a per-meal anabolic threshold of essential amino acids, particularly in terms of leucine (2.5–2.8 g/meal), should be achieved at least twice daily. Besides, vitamin D supplementation was found to result in improved muscle strength, particularly in old adults with low serum levels of the vitamin, and to promote muscle anabolism also through a positive interaction among all these nutrients.

Recent studies have demonstrated that the use of a muscle-targeted food for special medical purposes (a mixture of whey proteins enriched with essential amino acids, especially leucine, vitamin D and calcium) improves muscle mass and strength. However, although clinical trials in sarcopenia should address the recovery of physical functioning, the efficacy of the muscle-targeted food for special medical purposes on physical performance has never been evaluated in combination with physical exercise in a high-quality trial. Furthermore, there are no data on the economic benefits deriving from nutritional support in in-patient rehabilitation facilities.

# **Objective**

The aim of the study is to investigate the efficacy of a muscle-targeted nutritional supplementation (a mixture of serum proteins enriched with essential amino acids, especially leucine, vitamin D and calcium) on physical performance, functional and muscle mass recovery in older patients with sarcopenia admitted to an in-patient rehabilitation facility.

***2.1 Primary endpoint***

The primary endpoint will be the mean change in gait speed per month (m/s/month) during the 4-meter walking test.

***2.2 Secondary endpoints***

The following key secondary endpoints (change per month in physical performance outcome measures) will be investigated:

- chair-stand test
- Timed up and go (TUG) test
- Short Physical Performance Battery (SPPB)

The following secondary endpoints will be also addressed:

- change per month in handgrip strength
- change per month in Tinetti scale
- change per month in Barthel Index
- change per month in activities of daily living (ADL) score
- change per month in body weight
- change per month in appendicular muscle mass (AMM)
- change per month in skeletal muscle mass index (SMMI)
- change per month in cognitive status (Trail making test and Mini Mental State Examination [MMSE])
- change per month in quality of life (Short-Form 12-Item Health Survey [SF-12])
- the proportion of patients who improved their rehabilitation intensity profile
- the modality of discharge (home vs. institution)
- the overall economic benefits (using length of stay [LOS] and total duration of rehabilitation [minutes] as surrogate measures)
- safety of the intervention

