## *4.1 Inclusion criteria*

- age ≥65 years
- admission for physical rehabilitation
- sarcopenia (according to European Working Group on Sarcopenia in Older People [EWGSOP] criteria in terms of outcome of body composition by bioimpedance analysis [skeletal muscle mass/body weight  100, ≤37% in men and ≤28% in women], handgrip strength and gait speed)
- Mini Mental State Examination (MMSE) ≥18
- Written informed consent (patient or legal guardian)

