*Quality of life assessment*: participants will be tested with the Short-Form 12-Item Health Survey (SF-12), a short, generic health‐status measure reproducing the 2 summary scores of the SF‐36 - the physical component summary (PCS) score and the mental component summary (MCS) score – by addressing 8 health domains (physical functioning, role physical, bodily pain, general health, vitality, social functioning, role emotional, and mental health.

*Biochemical assessment*: venous blood samples will be drawn after an over-night fast and used for the evaluation of routine parameters (total blood count, glucose, transaminases, albumin, creatinine, blood urea nitrogen, serum electrolytes, transferrin, total cholesterol), as well as C-reactive protein and 25-hydroxyvitamin D (25(OH)D) levels.

*Assessment of complexity of assistance needs*: the rehabilitation profile system will be used to rate the complexity of assistance needed by the patient. Profiles are defined according to the assessment of 4 kinds of intervention and their interaction (general assistance, functional reactivation and recovery, medical support and social support). Patients entering an intermediate rehabilitation program as in-patients can be assigned any one of 5 different profiles:

- Profile 1: low assistance and medical needs; patient requires mainly general assistance;
- Profile 2: intermediate general assistance needs, but low medical needs; patient requires mainly general assistance, as well as functional reactivation and recovery;
- Profile 3: high general assistance needs and intermediate medical needs; patient requires mainly general assistance, functional reactivation and recovery, as well as intermediate medical support;
- Profile 4: high assistance and medical needs; patient requires general assistance, functional reactivation and recovery, as well as medical support on account of important concomitant diseases;
- Profile 4B DEMENTIA: high assistance and medical needs. Patient suffers from dementia and therefore requires a lot of general assistance, functional reactivation and recovery, as well as medical and social support provided by highly trained professionals.

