***8.2 Statistical analysis***

The efficacy analysis population will include the patients reaching the primary endpoint evaluation and it will be performed according to the intention to treat principle.

All patients consuming at least one serving of nutritional formula will be included in the safety analysis.

Descriptive statistics: Mean and standard deviation, range, median and quartiles will be calculated for continuous variables. Frequencies and percentages will be calculated for categorical variables.

Analysis of study endpoints: Expecting a treatment effect also on the LOS, changes over time in both primary and secondary continuous outcome variables will be normalized by the duration of observation in months. Changes will be calculated so that an improvement would result in a positive value in favor of the experimental formula (as either final - initial value or initial - final values).

*Primary endpoint* - The change in gait speed will be compared between groups with a generalized linear regression model using Huber-White robust standard errors to account for variance inhomogeneity. Then a series of supportive analyses of the primary endpoint will be performed. First, we will conduct a multivariable model, to adjust for potential confounders regardless of differences in baseline features, including gender, age and monthly change in energy intake, creatinine and in total cholesterol. Second, a conservative sensitivity analysis of the primary endpoint using the worst possible outcome of the study for patients dropping out will be performed.

*Secondary endpoints* - Group comparison will be performed for all secondary endpoints on a continuous scale using an unadjusted generalized linear regression model. For both primary and secondary outcome variables the mean change within groups will be also assessed. For secondary endpoints on a binomial scale, a generalized linear model for the binomial family will be used. For all endpoints the treatment effect (mean or frequency difference) and 95% confidence interval (CI) will be reported.

All statistical analyses will be performed using the software STATA 15.0 statistical software (Stata Corporation, College Station, TX).

Dropout

The following causes of dropout will be considered:

- Death

- Lost to follow-up (due to hospitalization or transfer to another setting of care)

- Withdrawal

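### Scoring the rehabilitation profile only as improved or not improved discards size of change and worsening, and leaves Profile 1 entrants unable to respond (minor)

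*Protocol*

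**What the plan says.** Protocol section 2.2 lists, below the three key secondary endpoints, "the proportion of patients who improved their rehabilitation intensity profile". The scale is described in section 6.1 under complexity of assistance needs: "Patients entering an intermediate rehabilitation program as in-patients can be assigned any one of 5 different profiles". The lowest level is "Profile 1: low assistance and medical needs; patient requires mainly general assistance". Profiles 2, 3 and 4 describe rising need. Profile 4B is given the same high level of assistance and medical need as Profile 4 and is set apart by dementia: "Patient suffers from dementia and therefore requires a lot of general assistance". The schedule in section 6 has the profile rated at baseline and at end of study.

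Section 8.2 gives the analysis: "For secondary endpoints on a binomial scale, a generalized linear model for the binomial family will be used", and "For all endpoints the treatment effect (mean or frequency difference) and 95% confidence interval (CI) will be reported". No covariate is named for binary endpoints. The only efficacy population stated is this: "The efficacy analysis population will include the patients reaching the primary endpoint evaluation". It is not restricted by baseline profile.

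**The concern.** The profile is an ordered scale measured twice in every evaluable patient. The endpoint keeps one bit of that information. Three things follow from the scale itself:

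- **Size is lost.** A move from Profile 4 to Profile 1 scores the same as a move from 4 to 3.
- **Worsening is hidden within this endpoint.** A patient who moves from Profile 2 to Profile 3 scores the same as one who stays in 2.
- **There is a ceiling.** A patient who enters in Profile 1 has no better category and scores as not improved in either arm.

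The first two hold whatever the entry mix. The third matters only to the extent that such patients are enrolled. At stake is the trial's ability to see an effect on the complexity of care, an outcome with a direct link to the resource question raised in the protocol's introduction.

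**Working it through.** **Inputs.** From section 8.1: 64 evaluable patients per arm and a two-sided 5% test. From section 8.2: the effect scale is a frequency difference. From section 6.1: Profile 1 is the lowest level of need. The protocol gives no improvement rates and no entry mix, so the rates and the share s below are assumptions.

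**The plan's own figure.** The 64 per arm is sized on gait speed with a standardized difference of 0.5. A two-sample t-test gives 63.8, so 64 per arm, with power 80.1%. The figure reproduces, but it was not set for the profile endpoint.

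**Effect of the ceiling on the difference.** Let p_T and p_C be the proportions improving among patients who can improve, and let s be the share who cannot, equal in both arms in expectation. The observed proportions are (1−s)p_T and (1−s)p_C, so:

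- difference = (1−s)(p_T − p_C), which shrinks by the factor (1−s);
- ratio = p_T / p_C, which is unchanged.

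**Effect on power.** With a = (1−s)p_T, b = (1−s)p_C and n = 64 per arm,

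power ≈ Φ( |a − b| / √{[a(1−a) + b(1−b)]/n} − 1.96 ).

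Assume p_T = 0.60 and p_C = 0.40:

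- s = 0: √[(0.24 + 0.24)/64] = 0.0866; 0.20/0.0866 = 2.309; power = Φ(0.349) = 63.7%.
- s = 0.05: a = 0.57, b = 0.38; √[(0.2451 + 0.2356)/64] = 0.0867; 0.19/0.0867 = 2.192; power = Φ(0.232) = 59.2%.
- s = 0.10: a = 0.54, b = 0.36; √[(0.2484 + 0.2304)/64] = 0.0865; 0.18/0.0865 = 2.081; power = Φ(0.121) = 54.8%.

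For comparison, an analysis restricted to patients who can improve has 64(1−s) per arm and keeps the full 20-point difference. For example, at s = 0.05 there are 60.8 per arm: 0.20/√(0.48/60.8) = 2.251; power = Φ(0.291) = 61.4%.

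| s | Difference, all patients | Power, all patients | Power, restricted |
|---|---|---|---|
| 0 | 20 points | 63.7% | 63.7% |
| 5% | 19 points | 59.2% | 61.4% |
| 10% | 18 points | 54.8% | 59.1% |
| 20% | 16 points | 46.5% | 54.2% |
| 30% | 14 points | 38.9% | 48.9% |

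A test with the variance pooled under the null gives slightly lower figures for all patients: 62.1%, 57.8%, 53.5%, 45.5% and 38.1%. Under another assumption, 70% versus 50%, the pooled version gives 63.9%, 58.5%, 53.4%, 44.0% and 36.0% for all patients. Restricted to patients who can improve, it gives 61.7%, 59.3%, 54.3% and 48.9% at s = 5% to 30%. The pattern is the same.

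**Effect of dichotomising, apart from the ceiling.** In a small illustrative simulation with an assumed profile mix and effect and no Profile 1 entrants, the baseline-adjusted ordinal analysis had power 70% and the dichotomy 58%. With 80 runs per scenario, the Monte Carlo standard errors are about √(0.70×0.30/80) = 5.1 points and √(0.58×0.42/80) = 5.5 points. This suggests the direction of the gain and does not measure its size.

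**The case against.** The strongest case on the other side has five parts.

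1. **The affected share may be close to zero.** Patients are admitted for physical rehabilitation and all receive a supervised exercise programme. Profile 1 is the only profile whose description does not include functional reactivation and recovery, so few entrants should be rated there. The sentence that any profile can be assigned describes the rating system, not this trial's intake. This stands, and it is why no size can be claimed as fact. It does not touch the loss of size and direction of change.

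2. **Profile 4B is not shown to be fixed.** A reader might infer that a patient with dementia can never leave 4B and so can never respond. The document does not support that: 4B is also described by level of need, and no rule bars re-rating to a lower profile. Nor does the protocol say that a move from 4B to 4 counts as improvement. The entry criterion "Mini Mental State Examination (MMSE) ≥18" should also keep this group small, although it does not exclude it.

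3. **There is no bias.** A reader might infer that the comparison between arms is distorted. Randomisation balances the share who cannot improve in expectation, a chance imbalance is covered by the confidence interval, and the ratio of proportions is unaffected. The test remains valid.

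4. **Worsening can be seen elsewhere.** Section 8.2 provides frequencies for categorical variables, and the Barthel Index, ADL score and Tinetti scale would show functional decline. So harm is hidden in this endpoint, not in the trial. It would likewise be wrong to say that the baseline profile goes unused: improvement cannot be scored without it. What is absent is adjustment for it.

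5. **This is detail for a statistical analysis plan.** The exact definition of improvement, the place of 4B and the denominator may well be set there, and their absence from the protocol is not the point made here. In particular, the protocol states no denominator specific to this endpoint. That Profile 1 entrants are counted follows from the general efficacy population. But the dichotomy, the binomial model and the frequency difference are choices that the protocol itself makes.

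**Conclusion.** The point holds as a minor matter of efficiency and information. The yes/no score discards the size of improvement, treats worsening as no change, and makes any Profile 1 entrant a non-responder. The first two are certain from the text. The third shrinks the frequency difference by (1−s). Under the assumed 60% versus 40% and 64 per arm, power falls from 64% to 59% at s=5% and 55% at s=10%. The larger losses at 20% or 30% are arithmetically right, but the protocol gives no reason to expect such shares. The conclusion that sensitivity is lost does not depend on the assumed rates; the figures do. The severity is minor because this is one of many non-key secondary endpoints and the trial is sized on gait speed.

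**What to change.** In sections 2.2 and 8.2:

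- Analyse the discharge profile as an ordered outcome, 1 < 2 < 3 < 4, with 4B tied with 4 because the protocol describes the same level of need for both. Use a proportional-odds model with treatment and baseline profile.
- Keep the proportion improved, with its frequency difference and confidence interval, as a readable companion. Take it over patients not in Profile 1 at entry, and define improvement as at least one lower level of need, so that a move from 4B to 4 does not count. Entry profile is a baseline characteristic, so this restriction keeps the randomised comparison.
- Report beside it the proportion who worsened, or a table of baseline by discharge profile in each arm.

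The cost is wording only, since the profile is already rated at both times. The downsides are that an odds ratio is less direct than a frequency difference, that the model adds a proportional-odds assumption, and that with about 128 patients some baseline-by-discharge cells may be sparse. The companion proportion and the table offset the first of these.

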# **Participants**

Consecutive, old adults, candidates for in-patient rehabilitation, who were found to have sarcopenia.

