***5.2 Nutritional intervention***

An individualized dietary program will be drawn up for each patient, taking nutritional and mastication issues, as well as any swallowing issues into consideration. In addition to hospital diet, subjects will be randomly allocated to receive twice daily:

a) Experimental formula: a whey protein-based food for special medical purposes enriched with leucine and vitamin D (Fortifit®, Nutricia). Each serving consists of 40 g of powder (vanilla or strawberry flavor), providing 150 kilocalories and containing 20 g of whey proteins, 2.8 g of leucine, 9 g of carbohydrates, 3 g of fat, 800 IU of vitamin D, and a mixture of vitamins, minerals (calcium, 500 mg), and fibers [17-20].

b) Control formula: an isocaloric formula consisting of 40 g of a flavored (vanilla or strawberry) powder containing maltodextrins.

The intervention formula will be reconstituted with 100-150 mL water and administered at breakfast and in the afternoon. In the event of dysphagia to liquids, the density of the reconstituted formula will be increased, as appropriate.

The actual supplement and control formula will be given in identical containers devoid of any labelling for at least 4 weeks (minimum duration of the rehabilitation) up to 8 weeks (maximum duration of the rehabilitation). Compliance with intake of nutritional interventions will be monitored by recording the number of servings consumed every day in a diary.

1. **Methods**

The assessments and the procedures to be performed throughout the study are summarized in the following table:

| ASSESSMENTS/PROCEDURES | BASELINE | END OF STUDY |
| --- | --- | --- |
| Inclusion/exclusion criteria | X |  |
| Informed consent | X |  |
| Medical history & demographics | X |  |
| Randomization | X |  |
| Anthropometry | X | X |
| Protein-calorie intake | X | X |
| Mini Nutritional Assessment | X | X |
| Physical performance | X | X |
| Physical function | X | X |
| Muscle strength (handgrip) | X | X |
| Muscle mass | X | X |
| Cognitive function | X | X |
| Biochemistry | X | X |
| Quality of life | X | X |
| Complexity of assistance needs | X | X |
| Compliance to nutritional intervention |  | X |
| Safety data |  | X |
| Modality of discharge |  | X |
| Total duration of rehabilitation |  | X |
| Length of stay |  | X |

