## *6.1 Assessments*

The following assessments will be performed throughout the study as indicated above:

*Medical History & Demographics.* Information will be collected on age, gender, main admission diagnosis, number of comorbidities and medications.

*Nutritional Assessment:* body weight (to the nearest 0.1 kg) and height (to the nearest 0.5 cm) will be measured according to standard procedures and body mass index (BMI) will be derived accordingly (*Anthropometry*). A trained dietitian will be responsible for the evaluation of calorie and protein intake. At study inclusion a 24-h dietary recall (with the aid of the caregiver) will be performed with the help of a food atlas, while at the end of study a calibrated dietetic spring scale will be used to weigh all foods served and returned on consecutive days. A computer program (DR3 v3.1.0; Sintesi Informatica Srl, Milano, Italy) will be used to estimate the energy and the macronutrient content of food consumed (*Protein-calorie intake*), including nutritional supplementation. Finally, nutritional status will be rated by means of the *Mini Nutritional Assessment* (MNA®), a brief questionnaire based on an anthropometric assessment (BMI and weight loss), a general assessment (lifestyle, medication, and mobility), and a dietary assessment (number of meals, food and fluid intake, self-assessment of autonomy of eating, and self-perception of health and nutrition).

*Muscle mass (body composition)*: in the screening phase, the presence of low skeletal muscle mass will be diagnosed [(skeletal muscle mass/body weight  100) ≤37% in men and ≤28% in women] using bioelectric impedance analysis (BIA 101; Akern s.r.l., Florence, Italy). Then, appendicular muscle mass (AMM) and total body skeletal muscle mass (for the calculation of skeletal muscle mass index [SMMI]) will be evaluated using Dual-energy X-ray absorptiometry (DXA; Lunar Prodigy, GE Medical Systems).

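### Discharge home versus institution is compared without recording where patients lived before admission, so any institution residents enrolled would shrink the difference and could not be identified

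*Protocol*

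**What the plan says.** Section 2.2 places "the modality of discharge (home vs. institution") among the secondary endpoints, below the three key secondaries. The schedule at the start of Methods marks "Modality of discharge" at end of study only, with no baseline counterpart.

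For history and demographics, section 6.1 states: "Information will be collected on age, gender, main admission diagnosis, number of comorbidities and medications". Residence before admission is not in that list, and neither the schedule nor any other described assessment names it. The nearest item is the Mini Nutritional Assessment, which is said to include "a general assessment (lifestyle, medication, and mobility"); residence is not mentioned.

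The Participants section enrols "Consecutive, old adults, candidates for in-patient rehabilitation, who were found to have sarcopenia". No criterion in 4.1 or 4.2 requires admission from home or excludes institution residents.

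Section 8.2 sets the analysis: "For secondary endpoints on a binomial scale, a generalized linear model for the binomial family will be used". It adds that for all endpoints "the treatment effect (mean or frequency difference) and 95% confidence interval (CI) will be reported". On the analysis set it says: "The efficacy analysis population will include the patients reaching the primary endpoint evaluation". No subset or covariate based on prior residence is named.

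**The concern.** A person who lived in an institution before admission may well go back there whichever formula was given. Under the stated endpoint that patient is recorded as institution, the same as someone who came from home and could not return. These are different outcomes, and the data the protocol lists cannot separate them.

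Patients whose destination is settled in advance carry no information on whether the formula helps people get home, yet they stay in the denominator and pull the frequency difference towards zero. By chance they may also be unequally spread between arms of about 64, and the listed data would not allow adjustment for that. A small or null result would be hard to read: it could reflect no effect, or a share of patients who could not have contributed one.

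**Working it through.** **The protocol's own figure.** Section 8.1 gives 64 evaluable patients per arm for 80% power at a two-sided 5% level and a standardised difference of 0.5. A two-sample t-test calculation gives 63.77, rounded up to 64, with power 80.1%. The figure reproduces. It concerns gait speed and is not touched by this point. The protocol states no rate and no power for discharge modality.

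**Inputs for discharge modality.**
- From the protocol: 64 evaluable patients per arm, two-sided 5% (section 8.1); frequency difference as the effect measure (section 8.2).
- Assumed, because the documents give no values: the share f of each arm admitted from an institution; that all of them return to one; and the proportions discharged home among patients admitted from home, p1 and p2.

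**Dilution.** The observed proportions discharged home are (1−f)p1 and (1−f)p2, so the observed difference is (1−f)(p2−p1). A 20-point difference becomes 19 points at f=5%, 18 at 10% and 16 at 20%. At f=0 nothing is lost.

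**Power.** Normal approximation, with q1 and q2 the proportions in the analysed group and n its size per arm:

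SE = √[q1(1−q1)/n + q2(1−q2)/n]; power ≈ Φ(|q2−q1|/SE − 1.96).

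Full efficacy population: q = (1−f)p, n = 64. Restricted to patients admitted from home: q = p, n = 64(1−f).

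Example with p = 65% and 85%, f = 10%:
- Full: q = 0.585 and 0.765, difference 0.18, SE = 0.0813, ratio 2.215, power 60%.
- Restricted: n = 57.6, difference 0.20, SE = 0.0785, ratio 2.548, power 72%.

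| Assumed home discharge | f | Difference, full population | Power, full | Power, restricted |
|---|---|---|---|---|
| 85% vs 65% | 0 | 20 points | 77% | 77% |
| 85% vs 65% | 5% | 19 points | 68% | 74% |
| 85% vs 65% | 10% | 18 points | 60% | 72% |
| 85% vs 65% | 20% | 16 points | 47% | 67% |
| 75% vs 65% | 0 | 10 points | 24% | 24% |
| 75% vs 65% | 10% | 9 points | 18% | 22% |
| 75% vs 65% | 20% | 8 points | 15% | 20% |

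**Sensitivity to the formula and the rates.** With a pooled variance under the null the values move by about 2 points or less. Under that formula, 90% versus 70% gives 81.5% at f=0 and 62.3% at f=10% (77.2% restricted); 80% versus 60% gives 69.9% and 56.0% (65.2%); 90% versus 75% gives 61.0% and 41.4% (56.4%). In every scenario with f above zero, restriction has the higher power despite the smaller denominator.

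**The case against.** The strongest reply is that the problem is conditional. Nothing in the protocol says that any institution resident will be enrolled. Guardian consent, the MMSE floor of 18 and the dementia rehabilitation profile do not show where patients live. A reader might infer that such patients are present in number and do dilute the endpoint; the documents do not support that, and at f=0 there is no loss. This stands. What remains is that the protocol neither rules such patients out nor collects what would show their absence.

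A reader might also infer bias between arms. That is not supported: with 1:1 randomisation prior residence is balanced in expectation, and the unrestricted difference is a valid effect in the population enrolled. The cost is a smaller difference, lower precision and possible chance imbalance.

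Nor is the comparison made in everyone randomised. It is confined to patients reaching the primary endpoint evaluation, and section 8.2 lists transfer to another care setting as a cause of dropout, so some moves to other care may leave the analysis altogether. Restricting by prior residence does not change that feature.

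The size also depends on a favourable assumption. A 20-point effect has no basis in the documents; with 10 points, power is about 24% at best and restriction adds little.

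Finally, the denominator and covariates of a secondary endpoint can be left to a statistical analysis plan, which is not shown. But such a plan can only use data that are collected, and the protocol does not provide for this item. It would be too strong to say that the gap could never be filled: residence before admission is a fixed fact that might be retrieved later, and the nutritional questionnaire may touch on living situation, though the protocol does not say so.

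**Conclusion.** The point holds as a cheap improvement to a lower-tier, unpowered secondary endpoint. The protocol compares discharge home with discharge to an institution without recording prior residence and without excluding institution residents, so two different outcomes share one code. If a share f of each arm comes from an institution and returns to one, the frequency difference falls by the factor (1−f).

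How much this matters cannot be settled from the documents, because neither f nor the home-discharge rates are given. Under 85% versus 65%, restriction gains about 6 points of power at f=5%, 12 at 10% and 21 at 20%; under 75% versus 65% it gains about 3 at 10% and 5 at 20%. The gait-speed endpoint and its sample size are unaffected.

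**What to change.** Add residence before admission (home or institution) to Medical History & Demographics in section 6.1, recorded before randomisation. In sections 2.2 and 8.2, specify that discharge home is analysed among patients who lived at home before admission, or adjust the binomial model for prior residence. Report the comparison in the full efficacy population alongside it.

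The subset is defined by a pre-randomisation characteristic, so the restriction itself introduces no selection after allocation. The cost is one extra baseline item and a somewhat smaller denominator for this endpoint. If no patient came from an institution, the two analyses coincide and nothing is lost.
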